**Outcome assessment**

*Outcome measures*

TFdi, p0.1, MV, RR, Vt (average of 3 readings, ^eighth^ hourly )

Arterial blood gas and associated values-Pa o2, PaCO2, pH, HCO3, p/F ratio (at least once a day)

Spo2, Fio2, ROX index, Subjective comfort and dyspnea scores – 8^th^ Hourly

VAS, RASS, Weaning (hours off NIV on high flow mask or face mask)- (mean values over 24 hours)

Intubation- Yes/ No: Days after randomization

Length of stay in ICU

Outcome at 28 days of admission

Incidence of excessive respiratory depression (PaCO2> 45 and pH < 7.2)

Incidence of difficult/ failed epidural insertion, catheter pullouts, and complications such as bleeding/ infection/ hematoma will be documented.

Timing of outcome assessment- - Every 8^th^-hour assessment / daily / one time as detailed above

Blinding- The assessor, patient, nurses, physicians, and treating team will be blind to group allocation. One member of the team not involved in research will administer the drug.

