**The research question**

Aim To compare the TFDi (primary endpoint), ventilator parameters, subjective comfort, rate of intubation, length of mechanical ventilation, length of ICU stay, and mortality of moderate to severe COVID 19 patients on noninvasive ventilation (NIV), with and without epidural morphine.

*Objectives*

To compare-

Thickening Fraction index of diaphragm TFdi, surrogate for the respiratory drive (primary outcome measure)

P0.1, mechanical ventilation (MV), respiratory rate (RR), Tidal volume (Vt), subjective comfort, the dose of sedatives needed, Visual Assessment of Pain (VAS), Richmond Agitation and Sedation Scores (RASS), time to intubation, length of mechanical ventilation, the incidence of VAP, incidence of sepsis, COVID 19 markers, length of stay in ICU, length of stay in hospital and mortality between the two groups.

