**The interventions**

A baseline assessment of all outcome measures as appropriate will be made. Normal body temperature, RASS of -1 or 0, and VAS < 4 will be ensured by administering Midazolam ( titrated to effect) or Paracetamol as warranted.

All patients will be turned lateral or sitting position, and an injection of LA be given at L2-3 or L3-4 space. An epidural catheter will be inserted under all asepsis and fixed to the skin in the intervention group. It will be fixed firmly with antimicrobial incise drapes covering at least the lower one-third of the back. For patients who appear fidgety, catheter tunneling may also be used.

The control group will have a sham catheter fixed precisely like the intervention group but not entering the epidural space. The fixation and dressing will be similar to the intervention group.

The intervention group will be administered Injection Morphine Sulphate once every 18-24 hours into the epidural space. The doses will be escalated daily (5-10mg), titrated to the effect: escalation limited by hypoventilation resulting in respiratory acidosis (pH <7.2).

The intervention will continue for a minimum of 2 doses and a maximum of 4 doses (96 hours) of morphine. It will be stopped at 120 hours, or if: the epidural catheter gets dislodged before the second dose, the patient is weaned off noninvasive ventilation to high flow mask for a continuous period of 12 hours or requires endotracheal intubation.

The patient will be followed up till death or 28 days after ICU discharge.

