**Post-recruitment retention strategies**

Participant retention- Follow-up will be till stay in the hospital or 28 days, whichever is longer.

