**Sample size**

Sample size justification A pilot study showed the mean TFDi in COVID 19 patients on PEEP 5 to be 45%(SD 15); To decrease mean fractional thickening of the diaphragm index by 30% after the dose of morphine with allocation in a 1:1 ratio, 21 patients will be needed in each group. Accounting for dropouts/ loss of data, 25 patients will be recruited in each limb.

*Statistical analysis*

Interim analyses are planned at 50% of sample recruitment, without unblinding to ensure that subjects are not being exposed to an unacceptable level of risk, whether the trial can be stopped early, check some of the assumptions that went into the original design and sample-size calculations of the trial (like within-group variability, recruitment rates, base event rates). The alpha spending strategy used will be one-fifth of the available 5 percent alpha at the interim analysis. i.e., the interim analysis p-value must be < 0.01 to stop the trial early and claim efficacy. Spend the remaining four-fifths of the 5 percent alpha at the end, or the end analysis p-value must be < 0.04 to claim efficacy. The two groups shall be compared for the mean TFdi (overall and 24^th^ hrly) by unpaired t-tests. Within-group comparison of TFdi shall be made (overall and 24^th^ hrly) by Repeated measures analyses.

Secondary outcomes- Intubation, Mortality, duration of mechanical ventilation, ICU stay, Subjective scores, Demographics, and severity of illness shall be compared by chi-square, t-tests, or nonparametric tests as suitable.

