**Sample size**

Sample size justification A pilot study showed the mean TFDi in COVID 19 patients on PEEP 5 and clinically optimal pressure support to be 45% (SD 15); To decrease this by 30% at 36 hours after the dose of morphine with allocation in a 1:1 ratio, 21 patients will be needed in each group.

Compliance and missing data- All analyses will be based on the groups as randomly allocated: an intention-to-treat analysis. A per-protocol analysis will also be done. The statistical significance will be taken as the 5% level for the top comparisons and the subsidiary comparisons, the 1% level. Patients with a P/F ratio > 150 at inclusion will be compared to those with lower values.

Data Storage- Because of the unique challenges of repeated data capture in COVID ICU, all repetitive data will be captured photographically and sent to a central data repository online to be categorized and stored by patient name and time of data capture (once every 8 hours), making in 14-time points of data capture for each patient. Data storage will be by blinded personnel.

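### Time to intubation is a listed comparison, but its recorded value exists only for intubated patients and the tests named give no stated way to keep the others in

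*Protocol*

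**What the plan says.** All references are to the Protocol.

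- **The research question, Objectives.** The comparisons between groups include "time to intubation, length of mechanical ventilation".
- **Outcome assessment, Outcome measures.** The item is "Intubation- Yes/ No: Days after randomization": an event indicator and, where the event occurs, its day.
- **Sample size, Statistical analysis.** The sentence on secondary outcomes begins "Secondary outcomes- Intubation, Mortality, duration of mechanical ventilation, ICU stay" and, after some further items, ends by saying that they "shall be compared by chi-square, t-tests, or nonparametric tests as suitable". Intubation is named there; time to intubation is not. No time-to-event method, censoring rule or rule for death before intubation appears anywhere in the document.
- **Sample size in the detailed methodology, Compliance and missing data.** "All analyses will be based on the groups as randomly allocated: an intention-to-treat analysis". A per-protocol analysis is added.
- **End of follow-up.** The interventions section says "The patient will be followed up till death or 28 days after ICU discharge". Post-recruitment retention strategies says "Follow-up will be till stay in the hospital or 28 days, whichever is longer". Outcome assessment has "Outcome at 28 days of admission". The section on intubation and mortality rates follows mortality to day 28 without naming the day from which it counts.

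**The concern.** For a variable held as a number of days, the usual reading of the named test families is a t-test or a rank-sum test. Either can use only patients who have a day. Patients who are weaned, discharged or otherwise never intubated have none, and they are the patients in whom the treatment may have worked. Those who die without intubation have none either.

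The groups left to compare are selected by an event that treatment may change, so randomisation no longer protects the comparison. A difference in mean days would mix any true effect on timing with a change in who gets intubated. At stake is a secondary outcome that clinicians would read closely: a subset result could be reported as a treatment effect, in either direction.

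**Working it through.** **1. What the documents supply.** They give no figure for time to intubation and no intubation rate. The sample size concerns TFdi. A 30% fall from 45 is 13.5 points, with SD 15. At an assumed 80% power, two-sided, the normal formula 2(z_alpha/2 + z_beta)² × 15²/13.5² gives 20 per arm at 5% and 21 at 4%. The t-based value at 5% is 20.4, rounded up to 21. The stated 21 therefore reproduces, but it says nothing about intubation. Its only use here is the planned recruitment of 25 per arm, 50 in all.

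**2. How many patients would have a day.** The expected number is 25 × (p_control + p_morphine). All rates are assumed.

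| Control / morphine intubated | With a day, of 50 |
|---|---|
| 30% / 20% | 12.5 |
| 40% / 20% | 15 |
| 50% / 30% | 20 |
| 50% / 35% | 21.25 |
| 60% / 40% | 25 |

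At 50% / 35%, 28.75 of 50 patients (57.5%) would drop out of a comparison of days.

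**3. Direction of the subset comparison.** Assumptions: early intubations have mean 1.5 days (exponential) and late ones mean 7 days (3 days plus an exponential of mean 4). Control has 25% early and 25% late. Morphine lowers the total to 35% in one of three ways and does not alter the timing of either type.

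Mean day among the intubated = (p_early × 1.5 + p_late × 7) / (p_early + p_late).

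Control: (0.25 × 1.5 + 0.25 × 7) / 0.50 = 2.125 / 0.50 = 4.25 days.

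| Morphine prevents | Early / late on morphine | Mean day on morphine | Morphine minus control |
|---|---|---|---|
| only late | 25% / 10% | 1.075 / 0.35 = 3.07 | -1.18 |
| both equally | 17.5% / 17.5% | 1.4875 / 0.35 = 4.25 | 0 |
| only early | 10% / 25% | 1.90 / 0.35 = 5.43 | +1.18 |

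Simulation of 4,000 trials with 25 per arm agrees with these means. The share of trials in which intubation looks earlier on morphine is 76-77% in the first pattern, 51-52% in the second and 27-28% in the third. In the first pattern, about 9% of trials were significant in the wrong direction at the 5% level. The fall in intubations is the same 15 percentage points in every row.

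**4. What the subset test can detect.** A second simulation (2,000 trials, constant hazards, follow-up to day 28, no deaths, two-sided 5%) compares tests on intubated patients only with a log-rank test on all 50. The hazard ratio is ln(1 - p_morphine) / ln(1 - p_control).

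| Control / morphine | Hazard ratio | t-test, intubated only | Rank-sum, intubated only | Log-rank, all 50 |
|---|---|---|---|---|
| 40% / 20% | 0.44 | 5% | 4% | 33% |
| 50% / 30% | 0.51 | 5% | 5% | 30% |
| 60% / 30% | 0.39 | 7% | 6% | 58% |
| 50% / 50% | 1.00 | 5% | 4% | 5% |

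The subset tests stay near their error rate even for large effects, because they ignore how many patients are intubated.

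**5. Fit of the passages.** The objective asks for a comparison of times. The recorded day is undefined for patients without the event. The intention-to-treat sentence requires everyone as allocated. A t-test or rank-sum test on the days cannot satisfy all three.

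**The case against.** A reader might infer that the protocol plans to test time to intubation by t-test or rank-sum in intubated patients. It does not say so. The analysis sentence names intubation, which the yes/no item and a chi-square test serve on all randomised patients, and no passage ties a t-test to the days. The log-rank test and Gray's test are themselves nonparametric, so the open wording could take them in. The intention-to-treat sentence also favours a reading that keeps everyone. Event status plus event day is just what a time-to-event analysis needs, so the data item is sound. All of this stands, and it means the subset comparison is a likely result of loose wording and not a stated plan.

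A reader might also infer that the subset comparison would point the wrong way. That follows only if morphine mainly prevents late intubations. The documents do not support that pattern over the others: dosing ends by 96 hours, while the assumed late intubations average day 7. The protocol also sets the 1% level for subsidiary comparisons, so the 9% of wrong-direction results at 5% overstates what would be declared.

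The remaining argument is that a censoring rule belongs in an analysis plan that is not shown. That is true of the detail. But the protocol names the test families itself, and read in the ordinary way they give no valid comparison of the days it sets out to compare.

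**Conclusion.** The point holds in limited form. Time to intubation is a stated comparison, its recorded value is undefined for patients never intubated, and the tests named, as ordinarily read, would compare a subset selected after randomisation, against the intention-to-treat rule. The outcome is secondary. The primary outcome and the yes/no comparison of intubation are untouched.

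The size depends wholly on assumed rates. At 50% v 35% intubated, the subset difference ranges from about -1.2 to +1.2 days for the same reduction in intubations, so its sign reflects which intubations are prevented and not whether the treatment helps. Under constant hazards, with assumed rates from 40% / 20% to 60% / 30%, the subset tests have 4-7% power against 30-58% for a test on all 50 patients. Neither set of figures predicts this trial. Together they show that the comparison of days among the intubated cannot be interpreted. The change should be made before unblinding, but the trial does not stand or fall by it.

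**What to change.** In Sample size, Statistical analysis, add that time from randomisation to intubation will be analysed in all randomised patients by cumulative incidence and compared by Gray's test. Death without intubation is a competing event, and patients alive and unintubated are event-free at day 28 from randomisation. State that any summary of days among intubated patients is descriptive only. Keep the yes/no comparison as it is.

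Then reconcile the end of follow-up with that horizon in The interventions, Outcome assessment, Post-recruitment retention strategies, and the section on intubation and mortality rates. An assessment at 28 days counted from admission ends before day 28 from randomisation for anyone randomised after the day of admission. Follow-up to 28 days after ICU discharge covers it.

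The cost is two or three sentences and one agreed horizon. Intubation status and day, and mortality to day 28, are already collected. At most, a few days' extra status would be needed where follow-up has been counted from admission.

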**Post-recruitment retention strategies**

Participant retention- Follow-up will be till stay in the hospital or 28 days, whichever is longer.

**Safety monitoring and adverse events**

Data and safety monitoring- Adverse effects will be documented and reported to the IEC.

**Data collection and management**

Data collection- Routine data will be extracted from the ICU records; Study-specific outcome data will be collected every eigh^th^-hour Data collectors will be distinct from the persons administering the epidural morphine/ vs. placebo- (in this case, air)

Photographic evidence will be kept of ventilator parameters, USG of the diaphragm, and subjective comfort and dyspnea scores at each data collection point and sent from inside the COVID ICU to the investigator who is not involved in the patient's clinical care and unaware of group allocation via Whatsapp.

Data entry- Will be done from the photographs and paper Case Report Forms (CRFs) into an Excel sheet by a researcher blinded to the group allocation.

For each time point, representative photographs (de-identified) will be kept for possible crosschecking and data validation as required.

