**Allocation of interventions**

Methods for randomization and stratification- The study research assistant will keep a central random numbers list. She will randomize according to the list available.

Methods for concealment of allocation- An opaque sealed envelope concealing the allotted randomization code will be dispatched to the ICU team.

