**EPIDURAL**

Baseline PT/ INR and platelet levels should be within an acceptable range to allow epidural insertion. Insertion catheter between 9 to 2 pm on the given day per the protocolized LMWH given at 7 pm on the units: or at least 4 hrs before the next dose of UFH and 12 hours after the last dose.

**Remove** the **catheter** a minimum of 4 -6 hours after a dose of UFH. Administer the next dose of UFH no sooner than 2 hours after **catheter removal**. Once-daily low-molecular-weight heparin (LMWH).

Daily site inspection (antimicrobial incise drapes transparent dressing) is done each time the drug/ sham injection is made. The injection port is kept well covered and sealed and brought to the side near the flank/ shoulder. The epidural catheters (True or Sham) will be in situ for a minimum of 2 doses or 48 hours, whichever is more, and a maximum of 4days (96 hours of catheter and 120 hours of observation).

All asepsis will be maintained for the control group as in the Intervention group, a Local injection anesthetic will be given at the L2-L3/ L3-L4 site, and the catheter will be taped tightly to the skin and dressing done to match the intervention group.

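### The treating team and assessor are declared blind, but the protocol's procedures for the envelope, air placebo, sham catheter and baseline assessment do not secure this

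*Protocol*

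**What the plan says.** The trial is labelled double-blind (Protocol, Overview of the trial). The blinding statement under Outcome assessment reads "The assessor, patient, nurses, physicians, and treating team will be blind to group allocation", followed by "One member of the team not involved in research will administer the drug".

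The procedures that bear on this statement are spread over several sections:

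- **Allocation of interventions:** "An opaque sealed envelope concealing the allotted randomization code will be dispatched to the ICU team".
- **The interventions:** controls receive a "sham catheter fixed precisely like the intervention group but not entering the epidural space".
- **EPIDURAL:** for controls, after a local anaesthetic injection, "the catheter will be taped tightly to the skin and dressing done to match the intervention group". The same section states: "Daily site inspection (antimicrobial incise drapes transparent dressing) is done each time the drug/ sham injection is made".
- **Data collection and management:** the study injections are described as "the epidural morphine/ vs. placebo- (in this case, air". It also says "Data collectors will be distinct from the persons administering" these injections.
- **Respiratory Drive and related parameters:** the researcher who inserts the true or sham catheter knows the arm and also makes the baseline assessment, including the baseline comfort scores. Later assessments are made by ICU trainees who are said to be blinded.

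**The concern.** A blinding claim is only as good as the steps that keep the code from the people named in it. Here the people named as blind include everyone at the bedside, while the code, the syringe and the catheter site all pass through the bedside with little or no described barrier.

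This matters because many of the trial's results depend on judgement there. Sedation and ventilator settings are adjusted to patient comfort, and TFdi is measured under whatever sedation and settings are in force. Weaning is left to the clinician's discretion (WEANING NIV SETTINGS). Some intubation criteria are subjective, such as lack of improvement in subjective scores and intolerance of NIV, and an oxygen trial before intubation depends on physician preference (CRITERIA FOR ENDOTRACHEAL INTUBATION). Discomfort and dyspnoea are subjective scales. A team that knows or guesses the arm could treat the two groups differently, and the trial could not separate that from an effect of the drug.

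**Working it through.** No figure in the protocol bears on this point, so the check sets the blinding statement against each procedure in turn.

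1. **Envelope.** The code is sent to the ICU team, which on a plain reading includes the nurses and physicians declared blind. The envelope is opaque and sealed, so sending it does not by itself reveal anything. What is missing is who may open it, and a statement that this person makes no treatment decisions for the patient.

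2. **Person giving the injection.** This person is kept out of the research and apart from data collection. Nothing places them outside the treating team. If they are a treating nurse or physician, the blinding statement contradicts the sentence that follows it.

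3. **Syringe.** Morphine is injected as a liquid and the placebo is air. Anyone who sees the syringe can tell the arms apart. The protocol does not describe preparation out of sight or masking of the syringe, nor does it say that bedside staff will see it.

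4. **Catheter site.** Three stated facts combine: the sham is taped to the skin, the dressing is transparent, and the site is inspected whenever an injection is given. The inspector is not named. If it is the person injecting, little is added to what that person already knows. If it is a bedside nurse, that nurse may be able to see the arm.

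5. **Baseline assessor.** This is the most direct conflict. Outcome assessment says that the assessor is blind. Respiratory Drive and related parameters says that the researcher making the baseline assessment is aware of the allocation. Both statements cannot hold for baseline, unless baseline is completed before the code is known, and the text does not say so.

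6. **Which outcomes are exposed, and how far.**
   - *TFdi, measurement:* partly protected. Pictures are stored for quantitative analysis and cross-checked by a blinded assessor, and ultrasound photographs go to an investigator unaware of allocation. The trainee at the bedside still chooses by eye the points of least and greatest thickness, and a later check of the stored picture cannot recover what was not stored.
   - *TFdi, co-interventions:* not protected if the treating team knows the arm, since sedation and support at the time of scanning are set clinically.
   - *Weaning, intubation, sedation dose, comfort and dyspnoea:* exposed, because each involves discretion or subjective report.
   - *Ventilator readings:* displayed and photographed, so recording is fairly safe. Like TFdi, they reflect the support and sedation chosen.
   - *Mortality:* its ascertainment is objective.

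**The case against.** The best defence is that the protocol has real safeguards. The envelope is sealed, and someone on site must open it because a true or sham catheter has to be placed. Fixation and dressing are matched, and both arms receive local anaesthetic at the same level. The injection port is covered and brought to the flank or shoulder, so an injection need not expose the entry site. TFdi is measured with the patient supine, so the back is out of view. Data collectors are separate from those injecting, later TFdi assessors are said to be blinded, and images and data entry are handled by blinded personnel. Intubation criteria are set in advance.

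Most of this stands, and it rules out two stronger readings:

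- A reader might infer that **blinding is undone**, because the envelope, the air and the dressing together must reveal the arm. The document does not support that. It does not say that bedside staff open the envelope, see the syringe, or can see through the dressing whether the catheter enters the skin. The last is a plausible inference, but not a stated fact.
- A reader might also infer that **the primary outcome is biased by some definite amount**. Nothing in the document gives a basis for any figure, and TFdi is the outcome with the most protection.

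What the defence does not answer is that its safeguards mainly protect measurement and data handling. Apart from the matched dressing and the sealed envelope, little in the text keeps the arm from the people who treat the patient. Nor does it resolve the conflict over the baseline assessor.

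**Conclusion.** The concern holds in this form: blinding of the assessor and the treating team is declared but not secured, and the sections on allocation, outcome assessment, data collection, the epidural catheter and respiratory drive need to be reconciled. The gaps are an envelope with no named opener, an injector not placed outside the treating team, an unmasked contrast of air and liquid, a transparent dressing with no named inspector, and a baseline assessor who knows the arm.

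The main risk lies in treatment decisions and subjective scores; the risk to TFdi is smaller and mostly indirect. The size of any bias cannot be estimated from the document. The conclusion assumes that bedside staff may be present when the injection is given or the site is inspected, which the protocol neither states nor excludes. The point should be fixed, but it does not make the trial unworkable.

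**What to change.** - **Envelope:** send it only to the unblinded catheter operator and the unblinded person giving the injection. State that neither takes part in the patient's treatment decisions or in any assessment after baseline.
- **Syringe:** prepare and give the drug or air out of sight of bedside staff, in identical syringes with opaque sleeves.
- **Site:** place a matched, removable opaque cover over the site in both arms. Assign routine inspection to the unblinded administrator at the times already planned, and state that anyone may lift the cover at any time for safety.
- **Baseline:** have a blinded trainee take the baseline scores, or complete them before the envelope is opened. Reword Outcome assessment and Respiratory Drive and related parameters so that they agree.

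The drug, the sham procedure and the frequency of inspection stay as they are. The cost is sleeves, covers and some rewording. The operator and administrator roles already exist, so no extra staff are needed, though they must be people not treating that patient. The downside is that other staff can no longer routinely view the site through the dressing, which is why lifting the cover for safety must be expressly allowed.
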